##### Physical activity and sedentary time

2.5.1.1

The Actigraph device (Actigraph GT3X+, Inc., Pensacola, FL, United States) was utilized for assessing PA at different intensities (light, moderate and vigorous) and sedentary time throughout the entire day. Participants were instructed to wear the monitor on their non-dominant wrist for eight consecutive days. Participants were advised to wear the accelerometer throughout the day (including sleeping time), except during aquatic activities or situations where exposure to water is possible. The screening and data collection procedures adhered to established protocols employed in previous research involving adolescents populations (42). Data will be extracted and analyzed using the GGIR package. Inclusion criteria for the analyses consist of: (i) a minimum of 3 valid weekdays of data and at least 1 valid weekend day of data; (ii) a minimum recording duration of 10 h per day (42, 43). The power analysis is performed based on MVPA during the school day, as it is the main variable of the study.

Additionally, to gather information on screen time throughout the day and the devices used, screen time was assessed using the specific items of the Youth Leisure-time Sedentary Behaviour Questionnaire (YLSBQ) (44). This questionnaire assessed the amount of recreational time per day spent on television, video games, computers, tablets, and smartphones, separately during weekdays and weekends. The student must choose whether they spend “0 min”, “30 min”, “1 h”, “2 h”, “3 h”, “4 h” or “5 h or more” per day on each of these behaviours.

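### The monitor is worn through sleep, but a day is valid on 10 h of any recording, so whole-day activity and sedentary minutes can be averaged over days with few waking hours observed

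*Protocol article*

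**What the plan says.** Everything that bears on this point stands in section 2.5.1.1 of the protocol article (Physical activity and sedentary time), under the primary outcomes.

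- Outcome: the device is used for "assessing PA at different intensities (light, moderate and vigorous) and sedentary time throughout the entire day".
- Wear: "Participants were advised to wear the accelerometer throughout the day (including sleeping time), except during aquatic activities" or other contact with water. The placement and period are given as "Participants were instructed to wear the monitor on their non-dominant wrist for eight consecutive days".
- Valid record: "a minimum of 3 valid weekdays of data and at least 1 valid weekend day of data".
- Valid day: "a minimum recording duration of 10 h per day".
- Processing: "Data will be extracted and analyzed using the GGIR package".

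No other section limits the 10 h to waking time, removes sleep from the count or sets a higher minimum for 24-hour wear. No setting for sleep detection, non-wear or imputation is given.

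**The concern.** Physical activity and sedentary time, taken here as waking behaviours, can be observed only while the student is awake and wearing the monitor. When a monitor is also worn in bed, the night alone can fill most or all of a 10 h recording threshold. The threshold then no longer guarantees that the waking day was observed.

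The whole-day outcomes are at stake. If minutes per day are averaged over valid days and non-wear is not imputed, a day with little waking wear enters as a full day with few active and few sedentary minutes. Both totals come out too low. Students with different wear habits are undercounted by different amounts, which adds noise. If the undercount is equal in both arms, it shrinks any true difference in daily minutes. If it were unequal, poorer wear would look like less sedentary time.

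**Working it through.** The article gives no figure to reproduce, because this is a data-acceptance rule. The check is hour arithmetic.

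**Inputs from section 2.5.1.1:** 10 h of recording makes a day valid; wear includes sleep; the smallest accepted record is 3 weekdays plus 1 weekend day, that is 4 days.

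**Assumption, not in the article:** sleep S of 7 to 10 h per 24 h.

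**Step 1. A day that just qualifies, with the full night recorded.**

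- Waking hours observed = max(0, 10 − S)
- Share of the waking day observed = (10 − S)/(24 − S)
- Share of the 10 h supplied by sleep = S/10
- Share of the waking day guaranteed if the 10 h had to be waking wear = 10/(24 − S)

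| S (h) | Waking day (h) | Waking hours observed | Share of waking day | Sleep share of the 10 h | Share under a 10 h waking rule |
|---|---|---|---|---|---|
| 7 | 17 | 3 | 17.6% | 70% | 58.8% |
| 8 | 16 | 2 | 12.5% | 80% | 62.5% |
| 9 | 15 | 1 | 6.7% | 90% | 66.7% |
| 10 | 14 | 0 | 0% | 100% | 71.4% |

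Sleep supplies more than half of the 10 h whenever S exceeds 5 h, so the conclusion does not depend on the exact value assumed.

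**Step 2. A milder case.** If the 10 h of recording were spread evenly over the 24 h, the waking part would be 10 × (24 − S)/24. That is 7.1 h at S = 7 and 5.8 h at S = 10. The figures in step 1 are therefore the lower end of what the rule allows, not what a typical day would look like.

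**Step 3. What one such day does to the smallest accepted record.** Assume 4 days weighted equally, three of them fully observed, minutes proportional to observed waking time, and no imputation. The undercount of the student's daily mean is (1 − share of waking day)/4.

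- Rule as written: S = 7 gives (14/17)/4 = 20.6%; S = 8 gives (14/16)/4 = 21.9%; S = 9 gives (14/15)/4 = 23.3%; S = 10 gives (14/14)/4 = 25%.
- A 10 h waking rule, with one day just qualifying: S = 7 gives (7/17)/4 = 10.3%; S = 8 gives (6/16)/4 = 9.4%; S = 9 gives (5/15)/4 = 8.3%; S = 10 gives (4/14)/4 = 7.1%.

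In this illustration, counting waking wear cuts the largest possible undercount from one poor day by half or more. The illustration is for one student. It does not estimate the error in the trial, because the number of such days is unknown.

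**The case against.** The strongest reply is that this is a condensed article. How the 10 h is counted, how sleep and non-wear are detected, and whether part-days at the ends are kept are processing settings that a full protocol or analysis plan may hold. The article also cites earlier work for the procedure and the threshold. That reply would succeed if the article were silent. It is not: it fixes a numeric acceptance rule, and that rule does not fit the wear instruction in the same paragraph. What stands is that the actual processing may already count waking wear, in which case one clarifying sentence closes the point.

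Four stronger readings are tempting, and the article does not support them.

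- *Minutes are in fact averaged over nearly empty days.* The article does not say how days are aggregated or non-wear handled. With 24-hour wear, most days should far exceed 10 h.
- *The bias is of a known, double-digit size.* One can obtain it by assuming that monitors are fitted and collected at the same clock time between 10:00 and 13:00 on the first and eighth days, with waking hours 07:30 to 23:00 and no imputation. Both part-days then qualify and together make one full day, so the weekday mean is (4 × 15.5 + 15.5)/6 = 12.92 h against 15.5 h, or 16.7% low. Over all eight recorded days it is 7/8, or 12.5% low. With collection at 09:00 the last day fails and the weekday mean is (4 × 15.5 + 14)/5 = 15.20 h, only 1.9% low. The arithmetic is right, but the article states no fitting or collection times, so none of these figures describes the trial.
- *The comparison of arms is biased.* The groups are not randomised, so differences between schools need not cancel. But nothing in the article shows that wear or visit times differ by arm or wave, and section 2.1 says both research groups worked to one common protocol for fieldwork and data handling.
- *The main result is affected.* The powered variable is MVPA in school hours (sections 2.2 and 2.5.1.1), and the Introduction's hypotheses on activity and sedentary time also concern the school day. This point covers only the whole-day measures.

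**Conclusion.** The point holds in a limited form. The valid-day rule and the wear protocol do not fit together: under 24-hour wear, 10 h of recording can be met with 0 to 3 waking hours if sleep lasts 10 to 7 h, where a waking rule would secure at least 59% to 71% of the waking day. Whole-day activity and sedentary minutes can therefore be undercounted and noisier than they need be.

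The hour figures rest on the assumed sleep duration and describe days that only just qualify. The number of such days, any correction in the software, and any imbalance between arms cannot be learned from the article. The change is worth making because it is cheap and specific, not because a bias of a given size has been shown.

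**What to change.** In section 2.5.1.1, for the whole-day activity and sedentary outcomes, replace "a minimum recording duration of 10 h per day" with: *at least 10 h of valid waking wear per day, after removal of sleep periods identified in GGIR*. Add that incomplete fitting and collection days are excluded from these outcomes, and that the same settings apply in both arms and at both waves. If the processing already works this way, say so in one sentence.

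Expressing minutes relative to waking wear time, or adjusting for it, changes what is estimated and is a matter of judgement. It is best kept as an optional sensitivity analysis.

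The cost is a wording change and reprocessing of data already collected. Some student-days will no longer qualify, and a few students will fall below the required number of valid days.

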#### Secondary outcome measures

2.5.2

##### Health-related physical fitness

2.5.2.1

To assess HRPF, the following tests belonging to the “ALPHA Fitness Test Battery” (45) were used:

###### 20-m shuttle run test

2.5.2.1.1

This test was used to assess cardiorespiratory fitness. Participants ran back and forth between marked lines on a track 20-m apart, matching the pace of an audio recording. The test started at 8.5 km/h and increased by 0.5 km/h per minute. It concluded when the participant stops due to fatigue or failed to maintain the required pace for two consecutive attempts. The participant’s score was based on the last stage completed.

###### Hand grip test

2.5.2.1.2

This assessment was used to assess upper body maximal isometric muscular fitness. Participants were measured with a validated hand-held dynamometer with an adjustable grip (TKK 5101 Grip D; Takey, Tokyo, Japan). First, the dynamometer’s grip was adjusted to the size of the participant’s hand (46). Throughout the assessment, participants stood in an upright position and grasp the dynamometer with one hand. They incrementally applied pressure to the dynamometer until reaching maximum force, sustaining this pressure for a minimum of two seconds, all while ensuring stability in the elbow, arm, and trunk. The test was conducted twice, with participants alternating between hands. The highest score attained with each hand was documented in kilograms, and the average value between the two scores is computed and stored for subsequent analysis.

###### Standing broad jump test

2.5.2.1.3

This test was used to lower body explosive muscular fitness. Participants positioned themselves behind a designated line with their feet shoulder-width apart. With a slight swing, they leapt forward as far as possible using both feet. If participants rested their hands on the ground or lift their feet upon landing, the test was considered invalid. This assessment was conducted twice, and the greatest distance achieved was measured in centimeters for analysis purposes.

###### Body mass index and waist circumference

2.5.2.1.4

Both variables were used to assess body composition. Body mass index was calculated as weight divided by height squared (kg/m^2^). The weight measurement was taken using an electronic scale (type SECA 861; range, 0.05 to 130 kg; accuracy, 0.05 kg), and the height measurement was taken using a telescopic height instrument (type SECA 225; range, 60 to 200 cm; accuracy, 1 mm) taking into account the Frankfort plane. In both measurements participants were barefoot. Waist circumference was measured with a non-elastic tape (SECA 200; range, 0 to 150 cm; accuracy, 1 mm). The tape was positioned in the frontal plane at the midpoint between the superior iliac spine and the costal border at the mid-axillary line. The measurement was taken twice, and the mean of the two measurements was recorded. If there was a difference between measurements greater than 1 cm, a third measurement.

##### Executive functions

2.5.2.2

The executive functions of inhibition, cognitive flexibility and working memory were assessed as main indicators of cognitive function. These were measured using the NIH Examiner programme (47) through the (i) Flanker task; (ii) Shifting task; and (iii) N-Back protocols, respectively.

###### Flanker task

2.5.2.2.1

This assessment measured response inhibition and cognitive control (48). During the task, participants focus their attention on a central fish among a row of five displayed on the screen. The central fish is marked either above or below it. Each trial lasts for 1,000 milliseconds, during which participants are instructed to promptly indicate the direction the central fish is facing.

###### Shifting task

2.5.2.2.2

This assessment measured cognitive flexibility (47). During the test, three figures of different colors are displayed on the screen, with one figure positioned at the top and one in each corner. The word “SHAPE” or “COLOR” appears on the screen, accompanied by auditory prompts from the computer. Participants are instructed to associate the top figure with one of the corner figures based on either its color or shape, depending on the prompt. If the word “COLOR” is heard, participants should select the corner figure with the same color as the top figure. Conversely, if the word “SHAPE” is heard, participants should select the corner figure with the same shape as the top figure.

###### N-Back

2.5.2.2.3

This assessment measured working memory (49). During the test, participants are presented with a series of screens. The first screen displays a white square in a specific location, followed by a number that participants are instructed to read aloud. Subsequently, a second screen appears featuring a white square, which may be located in the same position as the previous square or in a different one. Participants are tasked with recalling the location of the preceding square.

##### Academic indicators

2.5.2.3

###### School engagement

2.5.2.3.1

To evaluate this variable, the Spanish version of the Utrecht Work Engagement Scale (UWES-S-9) was used (50). The UWES-S-9 is composed of 9 items that reflect the three dimensions of engagement: (i) vigor; (ii) absorption; and (iii) dedication, each dimension is represented by three items that are evaluated through a Likert-type scale, ranging from “never” (0 points) to “always” (6 points).

###### Learning perception

2.5.2.3.2

Learning perception was assessed by the questionnaire developed by Abella et al. (51). The questionnaire consists of 8 items that measure two dimensions: “perceived learning” (items 1–4) and “satisfaction with learning” (items 5–8). Participants rate their agreement with each item on a five-point Likert scale, with “1” indicating “strongly disagree” and “5” indicating “strongly agree.”

###### Academic performance

2.5.2.3.3

This variable was evaluated through the marks reported by the schools in the three official evaluations of the academic year, specifically in December, April and June. The evolution of students throughout the school year is analyzed based on their grades in all subjects.

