### Study design

2.1

The MOVESCHOOL was a quasi-experimental study (trial registered on Clinicaltrials.gov: NCT06254638). This work was the protocol for the implementation of a school-based multicomponent intervention in the experimental group with pre- and post-intervention measures. MOVESCHOOL was a multi-center intervention whose management was designed to ensure effective collaboration and communication between the research groups. The research groups were composed of qualified researchers and graduates in PA and Sport Sciences from two universities [University of Extremadura (UEX) and University of Cadiz (UCA), Spain]. Both research groups followed a uniform study protocol for training, fieldwork, data collection and management, and quality control procedures. Continuous telematic communication was maintained throughout the study. A graphical summary of the study can be seen in the Supplementary file.

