### Interventions

2.3

The MOVESCHOOL study implemented a multicomponent school-based intervention over a period of 29 weeks. As we have explained in the introduction section, the study is based on the CAS framework (26). In this way, and also following the COM-B behaviour change model, the three basic elements (i.e., Capability, Opportunity and Motivation) were worked on with teachers and school leaders in a kick-off meeting, where the protocol to be followed in the project was explained to all the teachers and the staff from each school before the start of the intervention. This ensured that each school had a whole-school overview and for the study to have a global perspective of each center. Similarly, we worked together with school leaders and teachers with the aim to increase students’ PA levels during the school day by implementing the three arms of the intervention: PAL, AB, and AR (see Figure 2).

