#### Physically active lessons component

2.3.1

The PAL intervention consisted of integrating PA into academic lessons in different subjects that were typically sedentary. One subject was selected for each week of the intervention. Out of the total number of lessons taught per week in the selected subjects, one lesson per week for 29 weeks was dedicated to the PAL intervention. Each of the PAL was developed outdoors during the intervention. The PAL sessions lasted 60 min and were fully designed with tasks that incorporated PA throughout the session. According to the results of a pilot study we conducted in a previous study (39), participants spent an average of 29.78% of the PAL session time in MVPA. Since the activities of PAL implemented in both studies was similar, we expect PA intensities also to be similar. The teacher assigned to this intervention group, who has been trained beforehand, supervises the implementation of the strategies in their academic lessons with the constant support of the research team. Before each PAL lesson, the research team and the teacher met to determine the specific content to be covered and to jointly develop the activities to be included in the lesson. Examples of PAL activities can be found in Grao-Cruces et al. (40) and here.

Teacher training was conducted in the month prior to the start of the intervention. It consisted of two 60 min workshops, led by the members of the research team, aimed at providing teachers with a foundation for implementing PAL in their teaching. The training covered: theoretical foundations of PAL, main characteristics of PAL, applicability and examples of PAL in secondary school subjects.

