### Measures

2.5

Participants were assessed at baseline (October 2023) and post-intervention (May 2024). Post-intervention measure of accelerometers-based variables were assessed during the last weeks of intervention, due to the characteristics of the indicators. To minimize variability in assessments, all measurements were conducted in schools by researchers who have received prior training.

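### All three school marks used for academic performance postdate the start of the intervention, so December is an early-intervention value and not a baseline

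*Protocol article*

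**What the plan says.** Section 2.5.2.3.3 (Academic performance) takes this outcome from the "marks reported by the schools in the three official evaluations of the academic year, specifically in December, April and June" and adds that "The evolution of students throughout the school year is analyzed based on their grades in all subjects". It names no mark from before the study year.

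Section 2.1 (Study design) describes a "school-based multicomponent intervention in the experimental group with pre- and post-intervention measures". Section 2.5 (Measures) gives the dates: "Participants were assessed at baseline (October 2023) and post-intervention (May 2024"). It adds that "Post-intervention measure of accelerometers-based variables were assessed during the last weeks of intervention". Section 2.3 (Interventions) says the study "implemented a multicomponent school-based intervention over a period of 29 weeks", and section 2.3.1 repeats the length for the active lessons: "one lesson per week for 29 weeks was dedicated to the PAL intervention".

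Section 2.2 sets out a non-equivalent control group design, with five intervention and six control schools. Section 2.6 (Data analysis) plans a repeated measures model for each outcome and names gender, city and socioeconomic status as confounders to control. Prior attainment is not among them, nor is it in section 2.5.3 (Confounding variables). Better academic performance than in the control group is one of the hypotheses at the end of the Introduction.

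**The concern.** With schools not allocated at random, a value measured before the intervention is the main protection against differences that existed beforehand. Most outcomes have one from October 2023. School marks do not appear to: the earliest is the December mark, and the programme seems already to be running by then.

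If so, the marks can be used in two ways, each with a cost. Change from December subtracts whatever the programme had already achieved by December. A comparison of levels keeps any difference in attainment that the schools had before the study. A null change could then mean either no effect or an effect that had already appeared by December. A difference in levels could be an effect or a prior difference.

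**Working it through.** **Inputs.** Intervention length 29 weeks (sections 2.3 and 2.3.1). Baseline October 2023 and post-intervention assessment May 2024 (section 2.5). Marks in December, April and June (section 2.5.2.3.3). The article gives neither a start date nor the days on which marks were awarded, so both are varied below as assumptions.

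**Step 1: do the article's own dates fit together?** A start on 31 October 2023 plus 29 weeks ends on 21 May 2024. The stated length therefore fits between the October and May assessments.

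**Step 2: latest possible start.** Start = end − 29 weeks. With the latest end that fits a May assessment, 31 May 2024 − 29 weeks = 10 November 2023. If holiday weeks are not counted among the 29, the start moves earlier: 27 October with two such weeks, 20 October with three.

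**Step 3: weeks passed by the December mark.** Weeks = (mark date − start) / 7, and share = weeks / 29, with no holiday weeks:

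| Assumed end | Start | Weeks to 1 Dec | Weeks to 31 Dec | Share of 29 weeks |
|---|---|---|---|---|
| 31 May 2024 | 10 Nov 2023 | 3.0 | 7.3 | 10% to 25% |
| 15 May 2024 | 25 Oct 2023 | 5.3 | 9.6 | 18% to 33% |
| 1 May 2024 | 11 Oct 2023 | 7.3 | 11.6 | 25% to 40% |

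For an end in the second half of May, the range is roughly 3 to 10 weeks: 3/29 = 10% and 10/29 = 34%. An end on the first day of May would raise the upper limit to 40%, but it would leave only the first days of October for baseline testing.

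**Step 4: could December precede the start?** A start on 1 December would end on 21 June 2024, and a start on 22 December would end on 12 July 2024. Both run past the May assessment. On the stated dates, all three marks come after the start.

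**Step 5: effect on a December-to-June contrast.** Suppose the effect builds linearly over the 29 weeks, is still present at the June mark, and each mark reflects the student's state on its date. Then the between-group change retains 1 − w/29 of the effect, where w is the number of weeks passed at the December mark:
- w = 3: 1 − 3/29 = 0.90
- w = 10: 1 − 10/29 = 0.66

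An effect that appears fully in the first weeks would be lost from this contrast. If instead the December mark sums up work since the start of term, part of it predates the programme and the loss is smaller than the elapsed share.

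**Step 6: effect on a comparison of levels.** Gender, city and socioeconomic status do not measure attainment. Whatever attainment difference remains between the five intervention and six control schools after that adjustment stays in the estimate. The article gives no figure from which to size it.

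**The case against.** The strongest reply is that the article never calls December a baseline. It plans to follow marks over the school year, and with a repeated measures model that compares change between groups. Such a comparison removes stable school differences, including any stable difference in how strictly schools mark. Under linear build-up the remaining error is towards zero, so a positive finding would be conservative. This stands, and it sets the size of the point: the harm is attenuation of a change and uncontrolled prior attainment in a comparison of levels.

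A reader might go further and infer that the planned analysis cannot tell effect from prior difference at all, so that any result on marks would be uninterpretable. The article does not support that, for the reason just given. A null finding is less informative, but not meaningless.

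A reader might also infer that schools grade to different standards, or that marks are biased because teachers who deliver the programme also award them. The article says only that schools reported the marks. Both are plausible, but neither is documented, and unblinded marking is a separate matter from timing.

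Finally, the abstract lists academic indicators among the primary outcomes, while section 2.5.2 places them under secondary outcomes. That inconsistency is real, but it does not make this point weightier. The sample size section and section 2.5.1.1 both identify school-day moderate-to-vigorous activity as the main variable.

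**Conclusion.** The point holds in a limited form. On the article's own dates, academic performance has no pre-intervention value: the start was no later than about 10 November 2023, and the first mark came in December. That conclusion needs only the 29 weeks, the May assessment and the assumption that the programme did not run beyond May.

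The size is less certain. About 10% to 34% of the intervention had passed by the December mark, for an end in the second half of May and a mark on any day in December. A December-to-June contrast would then retain about 66% to 90% of a linearly building effect, and less of one that appears early. A comparison of levels avoids that loss but leaves prior attainment uncontrolled.

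This weakens one hypothesised outcome that the body lists as secondary. It does not touch the main variable.

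**What to change.** - Do not treat the December mark as a pre-intervention baseline. Describe it as an early-intervention value.
- Analyse the three marks with adjustment for the October 2023 mathematical fluency score, for all students. The assessment schedule in section 2.5 implies that this score is already held, so the cost is one added covariate. It is a three-minute arithmetic test and therefore only a partial stand-in for attainment across all subjects.
- Where consent and records allow, obtain previous-year final marks and use them as the pre-intervention value in a further analysis. The cost is a record request and a check that consent covers earlier records. Many 7th-graders' marks may be held by another school, so this may be incomplete for much of one grade and should not replace the analysis in all students.
- Report any December-to-June change as a change from an early-intervention value that may understate the effect.

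Making mathematical fluency the lead academic outcome is not needed. Data collection is described as done, and reordering outcomes now would be a late change made by preference.
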